### Data analysis

Data from in-depth interviews, FGDs, and key informant interviews will be transcribed, translated, and back translated then entered in qualitative data software (Atlas ti.8). We will then develop a coding frame using a grounded theoretical framework. Independent analysis will be conducted by different analysts and subsequent comparison between the developed coding matrices will be used to develop a reliability factor for the analysis. The trends from the emerging themes will be iteratively developed by repeatedly analyzing data collected at different time points. Verbatim generated alongside the code matrix will be used to support the emerging thematic framework.

Descriptive analysis of quantitative variables will be done using measures of central tendency (mean, median) and measures of dispersion (range, standard deviation), as appropriate. The inter cluster correlation will be computed. We will then conduct an exploratory analysis to compare outcomes by the sociodemographic, cultural, and economic characteristics (age, education, religion, marital status, life skills, wealth quintile, place of residence [urban or rural]) using the Rao-Scott chi-square test to see if there is any association. To determine the relative importance of these factors on the outcomes, generalized estimating equations, univariate, and multivariate logistic regressions will be used to adjust for clustering within the clusters. Results from the regression analysis will be reported as odds ratio and 95% confidence intervals.

For the quasi-experimental design, our hypothesis is that adolescent girls in the intervention study arm will have greater increases in FP utilization and improved knowledge and attitudes than girls in the control arm. We will estimate the intervention effect by subtracting the baseline FP utilization rate from the estimates at endline then calculating the difference between the comparison and intervention sub-counties (the difference-in-difference analysis). The difference-in-differences analysis assumes a common trend in the outcome in both the intervention and comparison area. We will measure potential confounders at baseline and endline and adjust our analysis for any compositional changes over time in these confounders. All statistical analysis will be considered statistically significant for *p*-values less than 0.05.

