### Study unit inclusion criteria and selection

Kisumu and Kakamega counties were selected as project areas in part because they are among the counties with the highest burden of teen pregnancy in Kenya—at 15 and 19%, respectively [9]. The study will focus on two sub-counties within Kisumu County (Nyando and Kisumu East) and two sub-counties within Kakamega County (Matungu and Navakholo). Within the identified four sub-counties, two wards have been selected in each sub-county, one as intervention (Kobura in Kisumu and Kholera in Kakamega) and the others as control (Bunyala West in Kisumu and Kajulu in Kakamega). The selection of the intervention ward is based on the poor reproductive and maternal health indicators coupled with low utilization of FP services among adolescents [9]. The wards were selected by the study team in collaboration with Ministry of Health officials after reviewing the wards’ service statistics. The intervention-comparison wards were selected to be similar with respect to sociodemographic characteristics and low utilization of FP services.

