#### Quasi-experimental design

We will conduct a cross-sectional household survey to collect quantitative data to measure knowledge, attitudes, practices, and uptake of ASRH services. The indicator used to compute the sample size was the FP services utilization rate among adolescents aged 15–19 years, using the most current data from the study areas obtained from the Kenya health information system. The FP utilization for both groups was computed and the lowest prevalence of the two was used in computing the sample size to guarantee the maximum possible sample size. An intra-class correlation of 0.03 was assumed resulting in a design effect of 1.87. The study is powered to detect a 15-percentage point difference between the two groups in each county, 95% confidence interval, with power of 80%. Furthermore, we account for a 10% loss due to possible non-responses and incomplete data. Using the parameters described, the sample size was determined to be 264 per arm (total 528) and 231 per arm (total 462) per arm in Kisumu and Kakamega counties, respectively, at each data collection period. A sample size of 990 participants will therefore be interviewed at baseline, and a similar number at endline. Community units are made up of villages, which, for the purpose of sampling, will be “cluster units.” Since the total number of units in each cluster unit and ward is known, villages will be randomly selected; eight villages in Kobura ward and eight from Kajulu ward in Kisumu County. In Kakamega, seven villages in Kholera ward and seven villages in Bunyala West ward. The sample size will be equally distributed among the selected villages in each ward. Households will be selected through systematic random sampling at an interval of 100–200 m from a particular landmark, until the required sample size is achieved for each ward. In households with multiple adolescents, the Kish method will be used to randomly select one individual from each household [10].

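### Two purposively chosen intervention wards are compared with two others, but only village clustering is costed and common trend is unchecked, so ward-specific change cannot be told from effect

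*Protocol article*

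**What the plan says.** All references are to the protocol article.

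- **Allocation.** Study unit inclusion criteria and selection names four wards: "one as intervention (Kobura in Kisumu and Kholera in Kakamega) and the others as control (Bunyala West in Kisumu and Kajulu in Kakamega"). The study team chose them with Ministry officials after looking at service statistics, not at random. On the intervention wards it says "The selection of the intervention ward is based on the poor reproductive and maternal health indicators coupled with low utilization of FP services among adolescents", and on the pairing "The intervention-comparison wards were selected to be similar with respect to sociodemographic characteristics and low utilization of FP services".
- **Cluster level.** Under Sampling, Quasi-experimental design, the cluster is the village: "Community units are made up of villages, which, for the purpose of sampling, will be" cluster units. There are 8 + 8 villages in Kisumu and 7 + 7 in Kakamega, and "An intra-class correlation of 0.03 was assumed resulting in a design effect of 1.87". Power is stated for each county, for a 15-point difference.
- **Rounds.** 990 girls are interviewed once at baseline and once at endline.
- **Analysis.** Data analysis takes endline minus baseline in each area and then the difference between areas. It states that "The difference-in-differences analysis assumes a common trend in the outcome in both the intervention and comparison area", plans adjustment for compositional change in measured confounders, and declares significance at p<0.05. Generalized estimating equations appear in the sentence on associated factors. The difference-in-differences sentences name no clustering method and no ward term.
- **Pairing.** The selection section gives "the others as control (Bunyala West in Kisumu and Kajulu in Kakamega"), whereas the sampling section has "eight villages in Kobura ward and eight from Kajulu ward in Kisumu County" and puts Bunyala West in Kakamega.

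**The concern.** The intervention reaches whole wards, so the ward is the unit of assignment. Villages within a ward share whatever else happens there in 18 months, such as a stock-out, another programme or a change in staffing. Sampling more villages or girls does not average that out. In each county, the level at which the study says it is powered, the contrast is one ward against one, so a local change and the intervention effect are fully confounded. Pooling gives two wards per arm, which barely helps.

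Common trend is the assumption that would rescue the comparison, but a single pre-intervention survey cannot test it. Adjusting for composition deals with who was sampled, not with how each ward was moving.

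At stake is the main conclusion: a drift in one ward could be reported as effectiveness of the combined model, with a p-value that contains no allowance for it.

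**Working it through.** **1. The plan's own figure.** 264/8 = 231/7 = 33 girls recruited per village. After the 10% loss, 33 × 0.9 = 29.7, about 30 analysed. Design effect = 1 + (30 − 1) × 0.03 = 1.87, exactly as stated. It is a village-level quantity and contains no ward component.

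**2. Inputs.**
- Analysed girls per arm per round: (264 + 231) × 0.9 = 445.5, taken as 445 (from the documents).
- Baseline FP rate p: not given. Assumed 18%, range 15% to 35%. Working back from the stated sample sizes (two-sided 0.05, no continuity correction) gives about 16% to 18% for Kisumu and 12% to 14% for Kakamega.
- SD of a ward's own change from baseline to endline, τ: not given. Assumed 3 to 5 points.
- Two-sided test (sidedness not stated).

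**3. Formula.** The village-level variance of the difference-in-differences is V = 4p(1 − p) × DE / n. With two wards per arm, ward changes add τ²/2 per arm, so τ² in total. The real level of a nominal 5% test is P(|Z| > 1.96 × √(V/(V + τ²))).

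**4. All analysed girls count.** V = 4 × 0.18 × 0.82 × 1.87/445 = 0.00248, so SE = 5.0 points.
- τ = 0: 5.0%.
- τ = 3: total SE √(0.00248 + 0.0009) = 5.8 points; threshold 1.96 × 4.98/5.82 = 1.68; level 9.3%.
- τ = 5: total SE 7.1 points; threshold 1.38; level 16.7%.
- Over FP rates of 15% to 35%: 10.0% down to 7.8% (τ = 3) and 18.3% down to 12.8% (τ = 5).

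**5. Only sexually active girls count.** Study outcomes restricts the primary outcome to them. Their share is not given; 30% to 50% is assumed, with p = 18%.

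| Share | Girls per village | DE | n per arm | SE (points) | Level, τ = 3 | Level, τ = 5 |
|---|---|---|---|---|---|---|
| 50% | 15 | 1.42 | 222.5 | 6.1 | 7.8% | 12.9% |
| 30% | 9 | 1.24 | 133.5 | 7.4 | 6.9% | 10.4% |

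The excess shrinks because sampling error grows, not because the ward problem goes away.

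**6. A fixed trend gap.** If the arms were simply on different paths, with SE 5.0 points, a gap of 5 points gives about 17% false positives and 10 points about 52%.

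**7. Can re-analysis repair it?** A t-test on four ward changes has 2 df (critical value 4.30), or 1 df if differenced within county (12.7). The 2-df test keeps its level in simulation (4.4% to 5.2%), but its power for a 15-point effect is only about 36% even with τ = 0. Permuting wards cannot give p below 2/6 = 0.33, or 2/4 = 0.50 paired by county. Within one county there is no ward-level degree of freedom at all.

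**8. The pairing.** Both sections name the same four wards and agree on their arms. They differ on the county of Bunyala West and Kajulu, so they define different within-county contrasts. A simple pooled estimate is unchanged.

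**The case against.** **The size rests on an assumed ward SD.** This stands. The documents give no ward-level variance, and with none and a true common trend the test keeps its 5% level. The figures are a conditional range, not a measured error rate.

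**Selecting poor performers means regression to the mean will look like effect.** A reader might infer this, but the documents support it only in part. Comparison wards were also chosen for low FP use, so much of any rebound is shared and cancels. What remains are ward changes unrelated to that matching, and any rebound tied to the poor indicators on which the intervention wards were picked.

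**The standard errors are too small because there are few villages.** A reader might infer this too. The article specifies no standard error for the difference-in-differences, and a small-sample correction is detail commonly left to an analysis plan. Nor would it address wards: a correction on village degrees of freedom still gives wards zero variance.

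**The assumption is stated openly.** True, and stating it is no fault. The weakness is that no check or sensitivity analysis is attached.

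**A pre-trend check may not be possible.** The article says ward statistics were reviewed and an FP rate was taken from the health information system. It does not say that a ward-level adolescent time series is held, so the check has to be conditional on one being available.

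**The county swap is a separate slip.** Agreed: it adds nothing to the type I argument, but it decides which wards the county estimates compare.

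**Conclusion.** The point holds in conditional form. Assignment is two wards against two, one against one by county. The planned variance is village-level only, and common trend is assumed with no means of checking it from the two surveys. A p-value below 0.05 on this basis speaks to these four wards over this period and takes ward-specific change to be zero.

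If ward changes have an SD of 3 to 5 points and the FP rate is 18% (both assumed), the real level is about 9% to 17% with all 445 girls per arm, or about 7% to 13% with 30% to 50% sexually active. With four wards, no re-analysis gives a usable 5% test that allows for ward variation.

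The stronger reading, that type I error definitely exceeds 5%, is not supported, because it depends on a variance that the documents do not give. The contradiction over the comparison wards' counties is plain in the text. This is a cheap improvement to the plan and its reporting, not a reason to reject the design.

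**What to change.** 1. Plan a comparison of pre-intervention FP service trends in the four wards from the health information system, where a ward-level series is available. State that facility counts measure something different from reported use among sexually active girls. Restrict it to the pre-intervention period, since data-quality work in both arms may alter later recording.
2. Report the difference-in-differences for each county as well as pooled. Add a sensitivity analysis over assumed ward-level change or trend gaps, for example SDs of 0, 3 and 5 points.
3. Word the conclusion as specific to these wards, and say that the p-value excludes ward-level variation. Agreement between the two counties should not lift this limit, since two null estimates share a sign half the time.
4. Reconcile the selection and sampling sections on which comparison ward lies in which county.

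The cost is a little analysis of routine data, one corrected sentence and a less strong conclusion. No new wards or fieldwork are needed.

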### Ethical considerations

In accordance with the principles governing research involving human participants, this study will ensure that respondents’ ethical rights are upheld. Ethical approval has been granted by the Kenya Medical Research Institute (number 651) and the Johns Hopkins University School of Public Health number (9227) institutional review boards. Approval by the county health management team and the health facility in-charges has also been granted. All adult participants will be required to give an informed written consent prior to participating in the study. Consent will be indicated by a signature or thumb print on the form. Parental permission for adolescents aged 15–17 years will be sought first, before the minor’s assent is sought. No minor will participate in the study until permission is provided by a parent/guardian and informed assent obtained from the minor. In addition, the data collectors and qualitative researchers will be experienced research staff who have a minimum of post-secondary education (college diploma) and who will undergo training on basic research ethics and study procedures, including maintaining confidentiality.

### Study status

Table 4 outlines the timeline for the study.

**Table 4 Tab4:**
[figure not shown]
Study timeline

### Dissemination of study findings

Dissemination will target multi-sectoral stakeholders and will be done at sub-county, county, and national level. This will include ministries of health, education, gender, and children’s services. The Ministry of Interior and Coordination of National Government, which is responsible for the police and administration, will also be involved. The results will be published in peer-reviewed journals and presented at national and international conferences.

## Discussion

Adolescent sexual reproductive health has gained traction in recent years. Sustainable Development Goal 3 aims to ensure universal access to SRH services by 2030, including FP, information and education, and the integration of reproductive health into national strategies and programs [11]. In addition, adolescents have now been included in the World Health Organization’s *Global strategy for women’s, children’s and adolescents’ health* (2016–2030), acknowledging the unique health challenges facing young people and their pivotal role, alongside women and children, as key drivers of change in the post-2015 era [12]. In Kenya, there have been milestones in policy regarding ASRH, however, a 2013 assessment of the 2003 policy revealed that there was limited dissemination of the policy and that it was not implemented equitably to all adolescents, especially the hardest to reach and most vulnerable populations [13]. In addition, barriers continued to exist that affect access to adolescent-friendly SRH services. As such, access to and utilization of ASRH services remains a challenge.

This study will evaluate the effectiveness of a combined approach to increase utilization of ASRH services. Results of the qualitative analysis and discussions with various stakeholder—such as teachers, health workers, and community representatives—will provide information on barriers to and enablers of use of ASRH services and the study team will develop recommendations on how to address the barriers and support enabling factors. The study will also provide information on the quality of ASRH services offered at health facilities, schools, and communities (outreaches) and provide recommendations on how services can be improved. Implementation of the study and results obtained from this study will be of direct benefit to the study sites and will contribute to improved utilization of ASRH services and reduction of teenage pregnancy in Kisumu and Kakamega counties. In additional, the study will generate evidence on whether a combined approach that targets several sectors—health, education, youth, and administration—works to improve utilization of ASRH services. The information generated from the study will also be beneficial for programming as it will identify underlying reasons as to why access to and utilization of ASRH services is low. Results will be helpful in improving programs that aim to address ASRH and reduce teenage pregnancy within the Kenyan context and in other similar low middle-income countries.

## Data Availability

Not applicable.

## Abbreviations

ASRH: Adolescent sexual and reproductive health
CORPS: Community Own Resource Persons
FGD: Focus group discussion
FP: Family Planning
IDI: In-depth interview
KII: Key informant interview
MOH: Ministry of Health
SRH: Sexual and reproductive health
STI: Sexually transmitted infections
